### Strengths and limitations

The main strength of this study is that it provides two different analytic perspectives on cost-effectiveness, allowing assessment of the robustness of results. It’s time frame is comparable to other community-based studies, although the full effect may not be captured as knowledge takes time to fully proliferate, supply systems mature through time, and changes in prescribing patterns can be a gradual process. A heterogeneous mix of patients will be included, enhancing the ability to generalize findings to other areas in India. Recall bias is minimized by asking only about episodes occurring in the last 2 weeks, in keeping with precedent from a previous study [57]. Overall, the quality of the data is high, with interviewers returning to households to fill gaps in missing data.

The main limitation of this study is that the study design of uncontrolled before and after studies is vulnerable to bias, such as secular trends, the Hawthorne effect [48], or regression to the mean [58]. However, the case for clinical effectiveness can be made based on evidence from randomized studies that have found reductions in the prevalence of diarrhea when providers were enabled to give zinc to children with diarrhea [10]. A CHERG review concluded that zinc causes a 23% reduction in diarrhea-specific mortality based on reductions in hospitalization rates, reasoning that this estimate was realistic as it was more conservative than reductions in all-cause or diarrhea-specific mortality found in other studies [14]. This evidence is consistent with the 2004 WHO/UNICEF endorsement of zinc for treating child diarrhea, which concluded that zinc reduces the severity and duration of acute diarrhea, and the number of episodes in the 2–3 months after treatment [8]. Since equipoise existed for the DAZT delivery strategy, but not for the effectiveness of zinc, the before and after study design was deemed to be the appropriate form of evaluation [59]. The intervention has since been rolled out statewide in Gujarat, and the final survey is underway in Uttar Pradesh.

Secular trends such as improvements in living conditions, access to safe water, and improved sanitation may have contributed to the decline in diarrhea prevalence in the DAZT study area [60]. However, secular trends may be less relevant for costs as economic growth is unlikely to drive prices for diarrhea treatment down. In addition, this study design is sensitive to sudden changes in the conditions of the study area [61]. The Hawthorne effect is a potential confounder, which would overstate the magnitude of the effect [48]. Regression towards the mean may be problematic [58], which means that if a study had high diarrhea prevalence at beginning, future measurements will be likely to be less extreme. The DAZT study found a 14% prevalence of diarrhea in 2011, while levels were 13% in 2005/6 in Gujarat [36] and were 9% nationwide [7]. Regression to the mean predicts that the prevalence would be lower in future surveys as downward changes would be more frequent than upward changes.

Limitations exist in that household data is based on self-report, reporting bias could have occurred, and long-term outcomes and programmatic outcomes such as quality are not measured. Some researchers argue that only children who receive the recommended 10–14 day course should be included in analysis. However, in the DAZT program, most children only received partial courses of zinc in addition to antibiotics and anti-diarrheal medications. Seasonal effects are possible given that each survey was given at a different point in the monsoon cycle across the years of the study. Limitations of principal components analysis are recognized, such as not evaluating the quality of assets, assuming the first principal component to be an adequate indicator of socioeconomic status, being a relative measure, and producing quintiles with variable arrays of asset ownership [53],[62],[63]. Finally, outcomes will not be evaluated according to severity, which could lead to outcomes such as children with fewer symptoms or shorter episodes having more favorable cost-effectiveness.

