**Table 2 Tab2:** **Sample sizes for each survey**

Survey	Number of participants		Dates
	Gujarat	Uttar Pradesh	
Starting point	4,200	3,889	March 22–May 10, 2011 Gujarat; April 1–June 21, 2011 Uttar Pradesh
Monsoon season			June through beginning of September^a^
Midpoint	1,072	1,790	September 1–October 8, 2012 Gujarat; May 24-October 4 2012 Uttar Pradesh
Endpoint	5,080	1,001	September 28–November 18, 2013 Gujarat; August 25–October 12, 2014 Uttar Pradesh

^a^Although peak diarrhea season lasts until November.

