**Conceptual framework based on Andersen and Newman [**[42]**].**

### Descriptive statistics

Descriptive statistics of the parameters (Table 3) will be calculated according to their means, confidence intervals, and *p*-values reflecting the extent of difference between arms. Comparisons will be made at the start and endpoint of the program. Stata svy commands will be used to account for clustering with *F*-tests used to evaluate the significance of differences between groups. As costs are not normally distributed, significance of differences between components listed in Table 4 at the start and end of the program will be calculated using confidence intervals with bootstrapped standard errors.

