### Net-benefit regression-based approach to cost-effectiveness analysis

A second approach to calculating cost-effectiveness will be taken according to net-benefit regression methods to control for imbalances in covariates arising from the non-randomized study design [21],[31],[32]. This method uses patient-level data of economic costs to caregivers and health outcomes, distributing program costs from the last year of the program evenly across children in the endpoint survey. A modification of the net-benefit statistic will serve as the dependent variable, given that outcomes are measured in terms of a health gap measure instead of health expectancy measure [50]. This formulation adds costs to outcomes expressed in monetary terms instead of taking the difference as is done in standard net-benefit calculations. The coefficient on a treatment variable that distinguishes between the starting point and endpoint of the program will be used to represent incremental net benefit. One sided *p*-values from the treatment variable will be used to construct CEACs, using results from a series of regressions that use different values for the ceiling ratio. Due to the non-normality in the distribution of residual values, a generalized linear model using a gamma distribution will be used. Huber-White robust standard errors will be used to address heteroskedasticity, and clustering will be accounted for consistent with study design. Data will be checked for non-linearities to assess whether use of a spline term improves model fit. The importance of influential data points will be checked using DFBETAs, excluding caregivers with the top ten DFBETA scores in sensitivity analysis. Calculations will be performed in Stata 13, using standards for good practice for using statistical regression models in economic evaluations [51].

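### The start and endpoint surveys share no calendar date in either state, so the episodes-based net-benefit coefficient mixes program with season, and the plan neither adjusts for this nor states the likely direction

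*Protocol article*

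**What the plan says.** Protocol article, Table 2, gives the survey dates:

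- Start: "March 22–May 10, 2011 Gujarat; April 1–June 21, 2011 Uttar Pradesh"
- Midpoint: "September 1–October 8, 2012 Gujarat; May 24-October 4 2012 Uttar Pradesh"
- Endpoint: "September 28–November 18, 2013 Gujarat; August 25–October 12, 2014 Uttar Pradesh"

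The same table places the monsoon at "June through beginning of September", with the footnote "Although peak diarrhea season lasts until November".

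The section on net-benefit regression defines the effect: "The coefficient on a treatment variable that distinguishes between the starting point and endpoint of the program will be used to represent incremental net benefit". Table 3 codes the program variable at two levels, initial and final survey, and lists no month or season variable. For the descriptive analysis, "Comparisons will be made at the start and endpoint of the program". Under Health outcomes, the net-benefit approach is confined to episodes averted, while the LiST approach takes incremental coverage from start to completion. The Abstract names the midpoint survey as a data source, but no analysis described in the article uses it.

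The Strengths and limitations section concedes that "Seasonal effects are possible given that each survey was given at a different point in the monsoon cycle across the years of the study". It gives no direction, adjustment or sensitivity analysis.

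**The concern.** Diarrhea episodes over a 2-week recall depend on the time of year. If all start interviews fall in one part of the year and all endpoint interviews in another, the start-versus-endpoint coefficient estimates the program effect and the seasonal difference together. Net-benefit regression was chosen to control for imbalances between the two surveys, yet this imbalance, visible in Table 2, is not among the covariates.

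The size, and possibly the sign, of incremental net benefit in the episodes-based analysis is at stake. The limitations text also gives directions for the Hawthorne effect and regression to the mean, both of which would flatter the program, but none for season, which probably works the other way. A reader is left with a one-sided picture of the bias. Running two methods on the same start and endpoint surveys will not reveal the problem.

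**Working it through.** The plan states no figure for seasonality, so there is nothing to reproduce. The check uses the Table 2 dates and sample sizes and the 14% prevalence in 2011 from Strengths and limitations, applied to both states as an assumption.

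**1. Calendar overlap within each state, ignoring year**

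| Pair | Gujarat | Uttar Pradesh |
|---|---|---|
| Start and endpoint | 0 days | 0 days |
| Start and midpoint | 0 days | 29 days (May 24 to June 21) |
| Midpoint and endpoint | 11 days (September 28 to October 8) | 41 days (August 25 to October 4) |

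Extending each window back by the 2-week recall still leaves start and endpoint with no shared day.

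**2. Survey days in the peak diarrhea season.** The footnote gives only the end of the peak. I assume it begins with the monsoon on June 1.

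- Gujarat: start 0 of 50 days. Endpoint 52 of 52 if the peak runs through November 30, or 34 of 52 if it stops on October 31.
- Uttar Pradesh: start 21 of 82 days (June 1 to 21). Endpoint 49 of 49.

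With one row per survey day, the correlation between survey and a peak-season indicator is 1.0 in Gujarat (0.69 with the earlier end of peak) and 0.72 in Uttar Pradesh.

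**3. What the midpoint can separate.** Fit an intercept, separate midpoint and endpoint effects, and a peak-season indicator.

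- Uttar Pradesh: rank 4 of 4, so program and season are separable.
- Gujarat, peak through November: rank 3 of 4, so they are not separable without assuming a time course for the program effect. If the peak ends on October 31 the rank is 4.

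Uttar Pradesh month effects do not carry over to Gujarat. The Uttar Pradesh surveys together cover April 1 to October 12. Outside that span lie 37 of the 52 Gujarat endpoint days (October 13 to November 18) and 10 of the 50 start days (March 22 to 31).

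**4. Illustrative size.** Observed endpoint prevalence = 14% × (1 − true reduction) × seasonal ratio. For a true 20% reduction:

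| Assumed seasonal ratio | Observed endpoint prevalence |
|---|---|
| 1.0 | 14 × 0.8 × 1.0 = 11.2% |
| 1.2 | 14 × 0.8 × 1.2 = 13.4% |
| 1.25 | 14 × 0.8 × 1.25 = 14.0% (effect cancelled) |
| 1.35 | 14 × 0.8 × 1.35 = 15.1% (apparent rise) |

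With no program effect, a ratio of 1.2 alone (14% to 16.8%) would be significant at two-sided 5% with probability 0.96 in Gujarat (n = 4,200 and 5,080) and 0.61 in Uttar Pradesh (n = 3,889 and 1,001). With an assumed design effect of 2 these become 0.75 and 0.36.

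**5. Precision of season matching in Uttar Pradesh.** Assuming even interviewing over each window, the matched cells are:

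- start: 3,889 × 29/82 = 1,375
- midpoint, early: 1,790 × 29/134 = 387
- midpoint, late: 1,790 × 41/134 = 548
- endpoint: 1,001 × 41/49 = 838

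The 95% half-width of the chained change (2011 to 2012 on the early dates, plus 2012 to 2014 on the late dates) is 1.96 × √[0.14 × 0.86 × (1/1,375 + 1/387 + 1/548 + 1/838)] = 5.4 points. The crude start-to-endpoint contrast gives 1.96 × √[0.14 × 0.86 × (1/3,889 + 1/1,001)] = 2.4 points. A design effect of 2 raises the chained figure to 7.7. A true 20% reduction is 14 − 11.2 = 2.8 points.

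**The case against.** The strongest reply is that the limitation is already disclosed. Table 2 prints the dates, the monsoon and the peak season; the Discussion names seasonal effects; and the Abstract accepts that an uncontrolled design limits policy conclusions. A sensitivity analysis may also sit in a fuller plan not shown here. The disclosure counts, and nothing is concealed. But the article fixes a two-level contrast and a covariate list without season, and it gives directions for other biases while leaving this one open.

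A second reply is that the bias is probably conservative. That is the likely direction for episodes, and it is worth stating. A conservative bias still distorts the size of incremental net benefit and could reverse its sign.

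Several stronger readings are tempting but not supported:

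- A reader might infer that survey and season are one and the same variable everywhere. This holds only in Gujarat, and only if the peak runs through November. The Uttar Pradesh start survey reaches into June.
- A reader might describe the endpoint as late monsoon. By Table 2 the Gujarat endpoint lies wholly after the monsoon, though within or largely within the peak diarrhea season.
- A reader might infer that the midpoint survey resolves the matter in both states. It does so in Uttar Pradesh. In Gujarat it shares no date with the start survey.
- A reader might extend the concern to the whole evaluation. The LiST and years-of-life-lost analysis is driven by coverage, which seasonal prevalence does not set directly.
- A reader might treat bias in either direction as equally plausible. A milder endpoint season runs against the footnote.

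The precision objection also stands. The chained Uttar Pradesh estimate is too wide to detect a 2.8-point effect, and it omits any program change between June 21 and August 25, 2012. It can serve as a check but not as a replacement for the main contrast.

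**Conclusion.** The concern holds for the episodes-based net-benefit regression. In each state the two surveys that define the treatment variable share no calendar date, and no season term is listed, so the coefficient mixes program with season. On the plan's own footnote the likely bias for episodes is against the program, and the article does not say so.

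The actual size cannot be derived from the documents. A ratio of 1.25 cancels a 20% reduction and 1.35 turns it into an apparent rise, but these ratios, the common 14% starting prevalence, the design effect of 2, the June 1 start of the peak and even interviewing are all assumptions. This is a worthwhile, inexpensive improvement to a disclosed limitation; it does not invalidate the evaluation.

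**What to change.** Keep the start-to-endpoint contrast as the main analysis and make these changes:

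1. In Strengths and limitations, state that moving from the start window to the peak season probably biases episodes against the program.
2. For Uttar Pradesh, add a sensitivity net-benefit regression that includes the midpoint survey, with interview month or season as a covariate.
3. For Gujarat, report the midpoint-to-endpoint contrast as a roughly season-matched check (11 days of overlap). Show the start-to-endpoint result over a range of assumed seasonal ratios, for example 1.0 to 1.35. Do not borrow Uttar Pradesh month effects.
4. Qualify the episodes-based conclusion if its sign changes across these analyses. Judge this against their intervals (about ±5.4 points for the chained Uttar Pradesh contrast against ±2.4 for the crude one, before any design effect), so that noise alone is not read as disagreement.

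No new data are needed. The cost is a little more analysis and season-adjusted estimates that are clearly less precise. In Gujarat, the start-to-endpoint result will continue to depend on an assumed ratio.

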### Targeting interventions according to subgroup

Cost-effectiveness according to subgroup can be assessed in the net-benefit regression framework as the coefficients on interaction terms between specific variables and the treatment variable. However, the case exists that zinc for diarrhea should not be targeted as it does not pose the threat of microbial resistance that is relevant to antibiotics and antimalarial medicines [64]. If widespread use of zinc reduces the use of antibiotics, microbial resistance to them may be slowed. In addition, zinc incurs only modest drug costs per child, and the costs of rationing treatment may outweigh the benefits of universal coverage [65]. In addition, universal coverage may be justified on equity grounds — while diarrhea affects people regardless of socioeconomic status, mortality preferentially affects the poor. Making treatments available according to patient subgroups is justified according to treatment effect, although is not justified according to demographic characteristics such as race [66]. However, information on key factors affecting effectiveness, such as or level of zinc status, were not collected. In addition, the data structure produces counterintuitive results as evaluating number of episodes treated at different service providers implies episodes averted when treatment seeking is reduced. For these reasons, cost-effectiveness according to subgroup will not be emphasized in this analysis.

### Generalizability

Results may be transferable to countries with similar health systems and epidemiological profiles. Because of differences in costs and similarities in efficacy of zinc across settings, the case has been made that cost-effectiveness is likely to vary more than effectiveness [22]. However, considerable heterogeneity in effectiveness has been found across settings, even within Asia [13], and results may be limited in their generalizability in this dimension as well. Other factors that may affect generalizability include ages of children, duration of illness, health systems infrastructure, receptiveness of health workers to changing treatment practices, and use of other medicines to treat diarrhea. Methodological assumptions may need adjustment as well, including the discount rate and study perspective. Descriptive statistics about the study setting will be presented to facilitate discussion about generalizability.

## Authors’ original submitted files for images

Below are the links to the authors’ original submitted files for images. Authors’ original file for figure 1 Authors’ original file for figure 2 Authors’ original file for figure 3 Authors’ original file for figure 4 Authors’ original file for figure 5

## Abbreviations

BMGF: Bill and Melinda Gates Foundation
CEA: cost-effectiveness analysis
CEAC: cost-effectiveness acceptability curves
CHAI: Clinton Health Access Initiative
DALY: disability-adjusted life years
DAZT: Diarrhea Alleviation using Zinc and ORS Therapy
DCP2: Disease Control Priorities Project second edition
FHI-360: Family Health International-360
GNI: gross national income
HTA: Health Technology Assessment
ICERs: incremental cost-effectiveness ratios
IMF: International Monetary Fund
IRB: Institutional Review Board
ISPOR: International Society for Pharmacoeconomics Research
JHSPH: Johns Hopkins Bloomberg School of Public Health
MI: micronutrients initiative
ORS: oral rehydration salts
PHCs: primary health centers
POUZN: Point-of-Use Water Disinfection and Zinc Treatment program
UNICEF: United Nations Children’s Fund
UP: Uttar Pradesh
WHO: World Health Organization
YLL: years of life lost
